### Parents Questionnaires

#### Parents’ Tolerance of Risk in Children’s Play

The Tolerance of Risk in Play Scale (TRiPS) [83] will be used to gather data on parents’ tolerances of risk during their children’s play. The TRiPS is a 31-item scale focusing on parents’ willingness to let children take risks in play. Parents select “yes” or “no” for questions such as “Would you let your child jump down from a height of 3-4 meters (10-13 feet),” or “Would you allow your child to play on equipment if you thought there was the potential s/he may break a bone?” The original English version of the TRiPS was validated using Rasch analysis and found that all items had mean square values within an acceptable range for internal (construct) validity and that internal reliability statistics were excellent (showed a high person reliability index of 0.87) [83].

For this study, the TRiPS was first translated from English to Norwegian by the author [name]. Then, all researchers in the project group discussed the translation to revise unclear wordings and adapt words and phrases to fit the Norwegian context. Next, the Norwegian version of the scale was back-translated to English by a professional translator, and the 3 versions (original English, translated Norwegian, and back-translated English) were discussed in the project group to ensure that the original meaning of the statements was retained in addition to being relevant and understandable for Norwegian children. In ViRMa, the TRiPS will be administered to all participating children’s parents, both mothers and fathers, via a web-based platform using the survey tool SurveyXact [84].

#### Background and Demographic Information

To gather background and demographic information, children’s parents, both mothers and fathers, will respond to items about children’s age, ethnicity, past injury history, living conditions (urban vs rural), access and use of nature, modes of traveling to school, participation in extracurricular physical activity (eg, sports), ECEC experience, family socioeconomic background, and other relevant information. The survey will be administered along with the TRiPS and CPBQ via a web-based platform using the survey tool SurveyXact [84].

During the study, children will respond to questions to capture their experiences and feelings while participating in the VR scenarios. For example, they will be asked, “Did you feel it was for real?” and “Have you ever tried VR before?”

### Data Collection Procedure

We will collect data in each school over the course of 2 to 3 weeks. We will install the VR equipment in a dedicated large room at each school, with enough space for a 7 × 6 m test area, with 4 SteamVR 2.0 Base Stations placed in each corner and room for children’s free movement within the space. The test area, with all 4 base stations as well as the VR goggles, will be calibrated with the normal calibrating procedures in SteamVR 2.0. We will identify participating children individually in their classrooms and escort them to the test area. Sensors (17 Xsens sensors) and trackers (5 Vive trackers, version 3) will be placed on the child’s body using Velcro bands. Next, we will introduce the child to the VR goggles and ensure that goggles are placed correctly on the head. VR goggles placement and eye-tracking measure sensitivity will then be calibrated through procedures in SteamVR 2.0. The child will enter a warm-up scenario in the virtual environment where they can explore a city park and familiarize themselves with being within, and moving around, the virtual world. During the warm-up, we will calibrate the Vive trackers to enable children to see their feet and also calibrate the Xsens sensors to ensure that motion-capturing measurements are correct. The last part of the warm-up scenario instructs the child about safety routines, as follows:

You will now be taken to three different scenarios where you should perform different tasks. The first scenario shows several traffic situations, including cars and bikes, where your task is to cross the street without being hit. The second scenario is a river in the forest where your task is to cross the river without falling into the water. Some tasks include balancing on a beam and some include stepping on stones to cross the river. The last scenario is an urban playground where you are allowed to do whatever you want and to play and explore the playground equipment as you like, for three minutes. I will be here walking next to you to make sure you don’t trip on the cable (attached to the goggles). If you ever want to quit the trial or skip to the next task, you can just let me know and I will help you.

### Ethics Approval

The Norwegian Social Science Data Services approved the ViRMa project (project 324155). We treat all data and information related to the project in accordance with the ethical guidelines of Norwegian Social Science Data Services. Child-friendly methods of seeking informed assent from children will be used, and informed consent will be obtained from the children’s parents or guardians. We will take careful measures to avoid placing research participants at risk by being sensitive to the specific challenges that arise in connection with involving children in research, as well as securing their right to withdraw from the research at any point. In the ViRMa project, we emphasize ethical responsibility in the presentation of all research results involving research participants in the project.

One possible undesirable effect of carrying out the data collection with VR scenarios is that children may become frightened of the simulated situations they encounter. A second risk is that children are overconfident, overestimate their risk management skills, and experience virtual falls in the VR scenarios that they find traumatic. Our pilot research suggested that these outcomes are both unlikely, but to address them, we will debrief all participating children, discuss their experiences, and remind them that their performance in VR tasks does not reflect reality.

### Analysis

The measures obtained from the VR, eye-tracking, and Xsens data include quantitative variables related to the child’s risk assessment, risk willingness, risk handling, and risk management. This study’s explorative and groundbreaking nature implies that an essential part of the analysis is to develop and validate new measures based on VR, eye tracking, and motion capturing. Consequently, the plan for data analysis is relatively general. The study therefore sets a conservative significance level (*P*<.01) to reduce the risk of type 1 error.

Cluster analyses will be applied to group children’s movement profiles based on the Xsens data divided into potential distinct groups by comparison of hierarchical agglomerative clustering methods: the Ward method and the between-groups average linkage method. For both methods, the squared Euclidean distance will be used as the measure of proximity. The final number of clusters will be determined by examining the agglomeration schedules and dendrograms generated for both techniques. Visual inspection of each cluster’s membership will be conducted to assess the utility of each potential cluster solution. Once the most statistically robust and theoretical relevant cluster solution is identified, a K-means iterative partitioning method will be applied to fine-tune the clusters [86,87].

Global measures on the child’s risk assessment, risk willingness, risk handling, and management will be established using exploratory factor analysis [88] drawing on data from VR, eye tracking, and motion capturing from the VR street crossing, river crossing, and playground tasks. RMS error of approximation (RMSEA), standardized root-mean-square residuals (SRMR), comparative fit index (CFI), and Tucker-Lewis index (TLI) will be used to evaluate and refine the established measurement models. Acceptable model fit is defined as RMSEA <0.1, SRMR <0.1, CFI >0.9, and TLI >0.9 [89]. Chi-square and chi-square difference tests will be conducted between the fitted and saturated models. However, no absolute thresholds for chi-square are set, following the sensitivity to sample sizes and the possibility that this measure may yield less precise estimates of the parameters [88,90]. Factor loadings will be investigated with the use of *R*² estimates (item >0.25) and standardized factor loadings (item >0.40) [88]. To validate the psychometric scales in the Norwegian context, factor analysis will be used. The scales with predefined subscales (SSSYC, Perceived Movement Skill, and CPBQ) will be validated using confirmatory factor analysis, and the TRiPS will be evaluated using exploratory factor analysis [88]. Acceptable model fit is defined as RMSEA <0.1, SRMR <0.1, CFI >0.9, and TLI >0.9. Factor loadings will be investigated with the use of *R*² estimates (item >0.25) and standardized factor loadings (item >0.40) [88].

Because the participating children are nested within schools, generalized structural equation modeling and multilevel regression analysis will be used in the primary outcome analysis to explore how children’s past risk experiences through play and daily activities are associated with their risk management. Children’s past risk experiences through play and daily activities will be measured primarily through the CPBQ and TRiPS, whereas measures related to the child’s risk management will be obtained from global measures related to risk management from the VR simulation. The child’s age, sex, and other relevant background and demographic information, as well as their sensation-seeking personality (measured through the SSSYC), will be included in the models.

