### Participants and Eligibility Criteria

We aim to recruit 500 children (50% girls and 50% boys) in second to fourth grade (7- to 10-year-old). This age group was chosen because we want to not only explore risk management skills among children as early in child development as possible but also consider practical matters such as the appropriate age to use current generations of VR goggles given their large size, weight, and functionality. VR technology develops rapidly, and studies involving even younger children would be an aim in the future. Further, children aged 7 to 10 years are likely familiar with navigating traffic and nature environments, while also remaining interested in exploring a playground, which reflects the tasks in the VR scenarios in this study. This is also an age group when children are more likely to behave independently and outside adult supervision, creating greater injury risk.

We aim to recruit children from both urban and rural primary schools in Norway because children in rural areas usually spend more time playing and being active in nature environments than children living in urban areas. The pilot study demonstrated that VR is a popular data collection method among children. To avoid excluding any children from a particular setting, we will select 4 primary schools from different parts of Norway and invite all children in the relevant age range at each school to participate. Inclusion criteria are as follows:

Between the ages of 7 and 10 years (grades 2, 3, and 4 in Norwegian schools)Informed consent obtained from parents to participateAssent obtained from the child to participate.

We will contact selected schools through the principal and ask if they are willing to participate. If they agree, parents will then be contacted through the school’s web-based information system, with information about the project and an electronic consent form provided. Children whose parents provide consent will then be placed on a participant list and names will be replaced with a random code. Children will also be asked for assent to participate, and if they decline, their name and code will be deleted.

Parents (both mothers and fathers) of children will be invited to complete the web-based survey.

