## Results

Funding to conduct the ViRMa project was confirmed in June 2021. From August 2021 to February 2022, the project group developed the VR scenarios, including eye-tracking technology and motion capturing, translated the scales, and developed the questionnaires. We will conduct the data collection from January 2023 to May 2023.

Four schools were recruited as data collection sites, with a total of approximately 660 students in second to fourth grade (7-10 years old). We aim to enroll 500 children and their parents for participation. The recruitment of children and parents for this study started in December 2022, and as of April 2023, a total of 433 parents consented for their children to participate.

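### School is the multilevel cluster but there are only four schools: the school variance is estimated very imprecisely, and a school-level covariate tested by Wald z at P<.01 would exceed its nominal error rate

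*Protocol article*

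**What the plan says.** The Analysis section names the nesting level and the method: "Because the participating children are nested within schools, generalized structural equation modeling and multilevel regression analysis will be used in the primary outcome analysis". The exposures in that analysis are mainly the CPBQ and TRiPS. Age, sex, sensation seeking and further background items enter as covariates. The same section "sets a conservative significance level (*P*<.01) to reduce the risk of type 1 error".

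The number of schools is fixed twice. Participants and Eligibility Criteria states "we will select 4 primary schools from different parts of Norway", and Results confirms it: "Four schools were recruited as data collection sites, with a total of approximately 660 students in second to fourth grade". The target is 500 children; Results reports that "as of April 2023, a total of 433 parents consented for their children to participate".

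Urban-rural appears in two roles. Participants and Eligibility Criteria makes it a reason for choosing schools, on the ground that rural children are more active in nature. Background and Demographic Information makes it an item that each parent answers: "living conditions (urban vs rural".

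**The concern.** A random school intercept estimates a between-school variance. With four schools that estimate has 3 degrees of freedom, or 2 once a covariate that is constant within school is in the model. Two things follow.

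- The parameter for which the multilevel model was chosen is poorly determined.
- A large-sample z test of a school-level covariate compares four units against a normal distribution, when a t distribution on 2 degrees of freedom is the natural reference.

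The second matters because urban and rural schools were sampled deliberately, so readers may expect an urban-rural coefficient with a P value. A chance difference between a handful of schools could then be reported as a finding at a threshold that the article presents as conservative.

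**Working it through.** **Inputs from the article.** Four schools; N = 433 consented (433/4 ≈ 108 per school, taking one child per consent) or the target of 500 (125 per school); nominal level .01. The article gives no power calculation, effect size or ICC, so there is no stated figure to reproduce.

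**Assumptions.** ICC from 0 to .20; two-sided test; REML or ML with a Wald z test; schools split 2:2 by urban-rural (a 1:3 split gave essentially the same results).

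**1. Precision of the school variance (3 df).** With n children per school, the estimate is zero when F(3, N−4) < 1/(1 + n·ICC/(1−ICC)). At ICC .02 and n = 108.25 the bound is 1/(1 + 108.25 × .0204) = .312, which has probability .183. At n = 125 the bound is .282 and the probability .161. By simulation, the zero-estimate rate is 28-30% at ICC .01, 6-7% at .05 and 2-3% at .10. At a true ICC of .05 (total variance 1), the central 95% of variance estimates runs from 0 to about .17.

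**2. Limiting error rate for a school-level covariate.** Four schools minus two parameters leaves 2 df. For t on 2 df, P(|t| > c) = 1 − c/√(2 + c²).
- REML: c = 2.576 gives 1 − 2.576/√8.635 = .123.
- ML divides the between-school sum of squares by 4 instead of 2, so c = 2.576 × √.5 = 1.821, which gives .210.
- The critical value that gives .01 on 2 df is 9.92.

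**3. Error rate at realistic ICCs.** Simulated rejection rate at nominal .01 (300,000 replicates, equal school sizes, variance truncated at zero), N = 433 / 500:

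| ICC | REML, % | ML, % |
|---|---|---|
| 0 | 0.7 / 0.7 | 0.9 / 1.0 |
| .01 | 3.8 / 4.2 | 5.6 / 6.4 |
| .02 | 6.3 / 6.8 | 9.7 / 10.7 |
| .05 | 9.5 / 9.8 | 15.5 / 16.3 |
| .10 | 11.2 / 11.3 | 18.7 / 19.1 |
| .20 | 12.0 / 12.1 | 20.2 / 20.4 |

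**4. Unequal schools, with a child-level exposure in the model.** Sizes 60, 90, 125 and 158 (total 433), 4,000 replicates, ICC .01 / .05 / .10, REML:
- urban-rural as a pure school label: 4.3% / 10.5% / 11.5%;
- urban-rural as the child's own residence, agreeing with the school label 90% of the time (assumed): 2.5% / 4.1% / 2.9%;
- a CPBQ-like exposure with an assumed ICC of .05: 0.9-1.2% in every REML and ML run. The Monte Carlo standard error is √(.01 × .99/4000) = 0.16 percentage points, so this is compatible with 1%.

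**5. Between-school confounding of the child-level coefficients.** A random-intercept model weights between-school information by w = (1−ICC)/(1−ICC + 108·ICC), which is .31, .15 and .08 at ICC .02, .05 and .10. If 5% of exposure variance lies between schools (assumed), that information contributes .05w/(.95 + .05w) of the coefficient: about 1.6%, 0.8% and 0.4%. When the variance is estimated as zero, w = 1 and the share is 5%.

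**6. Power of a valid test.** With a 2:2 split the standard error of the difference is s√(1/2 + 1/2) = s, where s is the estimated SD of school means within type. Significance at .01 would need a difference of about 9.9 s.

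**The case against.** The sentence that sets up the multilevel model concerns the CPBQ and TRiPS, which are measured per parent, and step 4 shows no inflation for such an exposure. No urban-rural hypothesis is stated, and the item could enter only among the further background covariates. It is reported by each parent and so may vary within a school. The estimator and any small-sample degrees of freedom could be set in an analysis plan that is not shown, and the article itself calls its plan fairly general. All of this stands, and it confines the point to school-level covariates.

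It does not remove the point. The article itself fixes school as the nesting level and four as the number of schools. An analysis plan could change the reference distribution but could not add schools.

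A reader might infer more than the documents support:
- *The school variance cannot be estimated.* It can, but very imprecisely.
- *The reported P values are 6 to 12 times too small.* That factor is a ratio of true to nominal rejection rate, not a multiplier on each P value. It needs an ICC of about .02 to .20, REML with Wald z and a covariate constant within school.
- *School differences pass straight into the CPBQ and TRiPS coefficients.* Step 5 puts the between-school share at about 5% at most under its assumption, and the limitations section already discloses non-random recruitment.
- *Leaving out the classroom level is an error.* The article says only "We will identify participating children individually in their classrooms". It does not say that class is recorded and gives no basis for the size of any classroom effect.

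**Conclusion.** The concern holds in a limited form. The school variance rests on 3 degrees of freedom and is unreliable. The primary child-level tests are not shown to be invalid. A term that is constant within school, tested by Wald z at .01, would reject about 4% of the time at ICC .01 and 6-12% at ICC .02 to .20 under REML. The rates are higher under ML (limit 21%), and there is no excess at ICC 0. Residence that mostly follows the school label gives about 2.5-4% under REML. These sizes depend on the assumed ICC, estimator, reference distribution and degree of agreement. The point is a cheap improvement, not a fault that undermines the primary analysis.

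**What to change.** - Enter school as a fixed effect (three indicators) in every association model, in place of the random school intercept. This removes between-school confounding from the child-level coefficients without relying on a variance from four units.
- Report any contrast between urban and rural schools descriptively, or test it outside those models on 2 degrees of freedom and say that power is almost nil. A pure school label cannot be estimated alongside the indicators.
- Parent-reported urban-rural residence may stay as a covariate; its coefficient then reflects differences within schools.
- Clustering by classroom is optional, if class was recorded.

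The cost is a change of analysis wording and 3 degrees of freedom out of about 430. Data collection does not change. The downside is that no meaningful formal test of urban versus rural schools remains, but four schools could not support one in any case.

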## Results

Funding to conduct the ViRMa project was confirmed in June 2021. From August 2021 to February 2022, the project group developed the VR scenarios, including eye-tracking technology and motion capturing, translated the scales, and developed the questionnaires. We will conduct the data collection from January 2023 to May 2023.

Four schools were recruited as data collection sites, with a total of approximately 660 students in second to fourth grade (7-10 years old). We aim to enroll 500 children and their parents for participation. The recruitment of children and parents for this study started in December 2022, and as of April 2023, a total of 433 parents consented for their children to participate.

## Discussion

### Principal Findings

This study will increase our understanding of child development. An essential goal of many educational, developmental, and pediatric health research studies is to understand how children’s characteristics, upbringing, and previous experiences influence their learning and ability to handle challenges. This study focuses on children’s abilities to manage risky scenarios and ties this to previous experiences. Using cutting-edge technology and previously developed measures to describe aspects of the child’s past experiences, this project addresses crucial topics related to children’s health and development. Such knowledge may guide pedagogical questions and development of educational and health-related interventions and reveal essential areas for focus in future studies.

One novelty of this study is related to technological and methodological advancements that may lead to new knowledge and discovery. The development and use of VR tools to explore how children handle real-life scenarios opens numerous avenues of research in different scientific fields. The integration of VR, eye-tracking, and motion-capturing technology has not been presented in published research to date and addresses many present scientific challenges. Moreover, the research represents methodological development in how VR technology may be paired with various measures in real time. Through life-like VR scenarios, it is possible to investigate children’s risk-taking in a controlled and safe environment, which may lead to substantial theoretical and empirical progress. A key ambition of the study is to develop and use technology and methods in a way that enables large-scale, replicable, international studies in other cultural contexts. Thus, the tools and technology developed must be standardized and easy to use.

From the perspective of contributions to developmental science, the project can lead to further scientific understanding of children’s motor competence and how it can be assessed. The combination of whole-body motion capture and VR embedded with tasks in which children can move around to explore and complete tasks represents a completely new research approach. With these features, children’s motor competence can be examined through the lens of movement behaviors emerging when individual, task, and environmental components interact. This strategy circumvents shortcomings identified within existing motor competence assessments and has broad implications for further work in designing and evaluating interventions and programs, as well as for research into underlying developmental processes and the role of influencing factors in the adaptive change within individuals as they work toward motor competence throughout childhood and adolescence.

The ViRMa project results will also benefit societal goals related to health promotion, education, parenting, and city and regional planning. A cross-cutting trend today is related to risk aversion resulting from the fear of injuries to children. Compelling theoretical perspectives suggest that reducing children’s possibilities to engage in risky situations may be counterproductive in terms of preventing injuries because children’s opportunities to learn to estimate and manage risk are diminished. If this study establishes empirical support for this hypothesis, it may impact how risk is addressed in crucial societal institutions like the family, early childhood education, and schools. Specifically, the ViRMa project aims to develop knowledge that may lead to healthier lives and fewer injuries through new knowledge about how children best learn to judge and manage risky situations in playful contexts. Through the acquisition of knowledge about children’s risk management in play, this study may benefit societal challenges related to children’s health and development and reduce economic burden to society stemming from the cost of unintentional injury treatment among children and young people [91].

